## **12.4 Study Discontinuation**

The study may be discontinued at any time by the IRB, the NIA, the OHRP, or other government agencies as part of their duties to ensure that research participants are protected.

## **13 PUBLICATION OF RESEARCH FINDINGS**

Publications will be operationally defined as manuscripts for publications; abstracts for platform or poster presentation at scientific meetings and other professional meetings; slides for presentation at scientific and other meetings; doctoral dissertations; and master's theses.

The goal of the publication policy is to encourage and facilitate publication of study results. The purposes of this policy are to ensure the following:

- PRIMA publication will be of the highest scientific quality
- PRIMA will be described in a consistent manner across publications
- Measures are reported in consistent ways across publications
- Proper acknowledgements are included
- Appropriate authorship credit is determined prior to submission of manuscripts for publication consideration.

Publications from PRIMA will be overseen by the PI and Co-Investigators.

## **14 ANCILLARY STUDY POLICIES**

An ancillary study will be defined as a study that (1) uses supplementary data that will be collected on participants who are recruited in PRIMA, over and above the data collection required by the PRIMA protocol, (2) collects biological specimens (e.g. blood) or performs diagnostic tests (e.g. bone density scans); and/or (3) collects data on subjects not enrolled in PRIMA but who may be compared to PRIMA subjects (e.g. participant who receive an alternative intervention). Ancillary studies will be distinct from databank studies, which use data previously collected on participants who are enrolled in PRIMA.

Ancillary studies will be reviewed and approved by the PI and CO-I's prior to initiation to ensure they do not conflict with the main study protocol. All approved ancillary studies will also be reviewed by the DSMB and NIA prior to initiation. If approved, the ancillary study PI will report to the DSMB on the same schedule as the main study. Review by the PI and Co-I's will also be required for presentation or publication of ancillary study results.

PRIMA investigators will be encouraged to consider ancillary studies and to involve other investigators, within and outside of PRIMA personnel. Participation in an ancillary

study will be subject to approval by the PI, Co-I's and DSMB. The following factors will be considered in determining approval of the proposed ancillary study:

1. Participant burden
  - a. The proposed study must be acceptable to the participants (e.g. in terms of time, discomfort, privacy, etc).
  - b. The proposed study must not reduce enrollment or hamper continued participation in the main study.
2. Study interference
  - a. The proposed study must not interfere with the other parts of the main study.
  - b. The proposed study must put little to no additional demands on the PRIMA resources.
3. The proposed study must be of the highest scientific merit.
4. The investigators must have adequate resources to effectively complete the ancillary study including:
  - a. Sufficient budget
  - b. Staff having the required expertise to meet the objectives of the project.

## Summary of Modifications from Original Protocol to Final Protocol

| Version
(date)          | Section | Brief Summary of Modification                                                                                                                                                                                                                              |
|----------------------------|---------|------------------------------------------------------------------------------------------------------------------------------------------------------------------------------------------------------------------------------------------------------------|
| Version 1.1
(2/9/2016)  | 4.1     | Removed inclusion criteria #5 – Not meeting physical activity recommendations defined as reporting less than 150 minutes of moderate intensity activity per week in the past month. This question will remain on phone screen so we can track information. |
| Version 1.2
(3/15/2016) | 5.4     | Updated strength training description—all subjects will completed hip extension and abduction strengthening as well as 1-2 other LE strengthening exercises at the PTs discretion                                                                          |
| Version 1.2
(3/15/2016) | 6.1     | Changed timepoint for “medical clearance to participate” to clinic screen; removed CHAMPS questionnaire; added Life Space Assessment and Pitt Sleep Quality Index for baseline, 12 week, 24 week, and 36 week timepoints                                   |
| Version 1.2
(3/15/2016) | 6.2.3   | Removed CHAMPS; added Life Space Assessment                                                                                                                                                                                                                |
| Version 1.3
(6/6/2016)  | 5.6.2   | Changed monthly phone calls to monthly check ins to be documented by study coordinator                                                                                                                                                                     |
| Version 1.3
(6/6/2016)  | 5.7     | Updated requirements for schedule intervention visits to include first session 8-14 days after baseline testing; added randomization timing to details                                                                                                     |
| Version 1.4
(8/19/2016) | 8.5-8.7 | Updated information on who RAEs should be reported to and in which order. SAEs that are not related to the protocol will not be considered RAEs.                                                                                                           |

**Original statistical analysis plan** as published in Brach et al, 2020^1 and documented in [clinicaltrials.gov](https://clinicaltrials.gov).

*Overview.* All statistical analyses will be performed based on the intention-to-treat philosophy. First, the baseline pre-intervention values of participant characteristics and measurements will be compared between the two arms with and without consideration of gait speed stratum using analysis of variance, Kruskal-Wallis, chi-square and/or Fisher's exact tests, as appropriate, depending on type and distribution of variables. No significant differences are expected due to randomized intervention assignment and the large sample size, but any found to be significantly different will be noted and accounted for, by controlling for them as additional covariates in supplements to the main analyses. We will not alter the main analyses to preserve its a priori and predictable nature. Next, main analyses to address the specific aims and hypotheses will be performed. If an analysis of residuals reveals violations of standard assumptions of linear models, we will use a Box-Cox transformation to the response variable before fitting the models. Multiple imputation will be used to account for any missing data in the main analysis. Finally, many exploratory follow-up analyses will be performed as outlined below.

*Main Analysis.* We will fit a series of linear mixed models using the SAS® MIXED procedure with change from baseline in each of the continuous outcome measures as the dependent variable; intervention arm (standard/standard plus), follow-up time point (12-/24-/36-week) and their interaction as fixed effects; baseline value of outcome as an additional fixed effect covariate; and a participant random effect. We will appropriately construct means contrasts to compare the intervention gains at 12, 24 and 36 weeks. The tests of significance at  $\alpha=0.05$  for the 12-week gait speed means contrast will be considered the formal test of the primary hypothesis. Next, we will repeat the above mixed model analysis entirely, but with

stratification by baseline gait speed (<1.0/1.0+ m/s). Statistical significance of 24- and 36-week means contrasts and other outcomes will be considered as tests of the secondary hypotheses involving process, activity and participation outcomes as well as persisting effects.

*Exploratory Analyses.* To examine subgroup-specific intervention effects, we will repeat the main analyses after stratification by various other baseline participant characteristics (besides baseline gait speed) to identify, if any, subgroups which are most/least likely to benefit from interventions. A priori, we anticipate that stratification by baseline walking confidence and cognitive function may show differential gains. We are aware that any definitive subgroup analyses should be supported by strong evidence in the form of a significant interaction effect. Tests of interaction generally have low statistical power, and it is not a main goal in the present trial to recruit a large number of participants required for definitive subgroup analyses beyond the already included pre-planned subgroups based on baseline walking speed. Thus, we plan to interpret our subgroup analyses with caution and an exploratory rather than a confirmatory philosophy, whose results are to be confirmed in a larger subsequent trial.

#### **Final Statistical analysis plan (current, submitted manuscript)**

See published protocol for details. We compared baseline characteristics between groups using independent samples t-, chi-square and Fisher's exact tests. For main results, we performed an intention-to-treat analysis with multiple imputation for missing data. We fit linear mixed models with change from baseline in each continuous outcome measure as the dependent variable; intervention arm, follow-up time point and their interaction as fixed effects; baseline value of outcome as a fixed effect covariate; and a participant random effect. For outcomes based on accelerometers, wear time was an additional covariate. We constructed means contrasts to

compare the intervention gains at each of the follow-up time points. We repeated the analysis with gait speed stratum and stratum  $\times$  intervention as additional fixed effects to obtain stratum-specific findings. SAS® version 9.4 software (SAS Institute, Inc., Cary, NC) was used.

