### **10.1 Main Analysis.**

First, we will fit a series of linear mixed models using the SAS® MIXED procedure with change from baseline in each of the continuous outcome measures as the dependent variable; intervention arm (standard/standard plus), follow-up time point (12-/24-/36-week) and their interaction as fixed effects of interest; baseline value of outcome as a fixed-effect covariate; and a subject random effect to account for multiple follow-up assessments from the same patients over time and resulting stochastic non-independence of observations. We will appropriately construct means contrasts to compare the two intervention gains at 12 weeks (immediate effect), 24 weeks (delayed effect) and 36 weeks (sustained effect). Test of significance at  $\alpha=0.05$  for gait speed outcome at 12 weeks will be considered the formal test of the primary hypothesis 1.1. Second, we will repeat the above mixed models analysis entirely, but with stratification by baseline gait speed ( $<1.0/1.0+$  m/s). Tests of significance for gait speed outcome at 12 weeks in each of the two strata will be considered formal tests of the primary hypothesis 1.2. Statistical significance of at 24- and 36-week comparisons or other outcomes will be considered as formal tests of the secondary hypotheses involving activity and participation as well as delayed and sustained effects. Third, we will repeat the analyses after controlling for covariates identified a priori or found to be different between intervention arms by including them as additional fixed effects in supplements to main analyses.

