### **10.5 Sample Size Adequacy**

Sample size is estimated based on preliminary data from our pilot studies; our ability to detect statistical significance in two-tailed tests conducted at the  $\alpha=0.05$  level unless otherwise noted; and conservative expected dropout rates of 10, 15 and 20% during the 12-, 24- and 36-week follow-up. Thus, we conservatively anticipate 55, 52 and 49 participants to complete the 12-, 24- and 36-week assessments, respectively. We used standard sample size and power computation methods available in the literature and commercial software (PASS®; Number Cruncher Statistical Systems, Inc., Kaysville, Utah).

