#### **10.5.1 Primary Outcome**

Our primary outcome on which the sample size justification is based is gait speed. Our preliminary data suggest a conservative estimate of between-subject standard deviation in baseline gait speed is 0.17 m/s and baseline to follow-up change in gait speed is 0.15 m/s. Moreover, a meaningful change in gait speed is approximately 0.10 m/s. With the proposed number of 124 in each intervention, we will have >99% power to detect statistical significance of a between-intervention difference of such magnitude in 12-

week change (primary hypothesis 1.1). We anticipate that approximately half of the participants will belong to the slower baseline gait speed stratum. Thus, with the expected number of 62 participants within each arm within each stratum, we will be able to detect statistical significance of a between-intervention difference in 12-week change within each stratum (slower/faster baseline gait speed) with 96% statistical power (hypothesis 1.2). For 24- and 36-week gait speed change, we will have 92% and 90% statistical power, respectively, within each stratum (delayed effect and sustained effect hypotheses). If the anticipated split between slower and faster walker strata turns out to be no worse than 55%-45%, we will still have  $\geq 90\%$  power for both strata for hypothesis 1.2; and if it is no worse than 67%-33%, we will still have  $\geq 80\%$ .

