## 10.6 Treatment Assignment Procedures - Randomization

We will use the high quality pseudo-random deviate generator available in SAS® (SAS Institute, Inc., Cary, North Carolina) to randomize participants to standard or standard-plus interventions in a 1:1 ratio, stratified by whether a slower ( $<1.0$  m/s) or faster ( $\geq 1.0$  m/s) walker at baseline. Within each baseline gait speed stratum, we will do a blocked randomization to force continued approximate balance between the numbers of subjects in each arm during recruitment. The block size will be randomly selected to be 4 or 6 to prevent personnel from predicting treatment arm. For example, if the first two participants are randomized to active interventions, the assignment of the next participant cannot with certainty be predicted to be control. The study statistician will create randomization schedules for the two strata which contains a randomization sequence number (different from a participant's study identification number) and assigned arm. Randomization sequence numbers will be readily distinguishable between the strata (ie. starting from 4001 for slower and 8001 for faster baseline walkers). Then he will pass the randomization schedules to data management personnel so that they can be incorporated into the data management system itself. At

the time of randomization, research personnel will indicate the eligible participant to be randomized in the data management system. The system will first determine the stratum of the participant being randomized, and then use the next available randomization sequence number for that particular stratum to determine the intervention assignment based on the schedule constructed by the study statistician, record the intervention assignment in a restricted location in the database inaccessible by the blinded personnel, and retire the used randomization sequence number and randomized participant number from the randomization process. Personnel assessing follow-up outcomes will be blind to intervention assignment.

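### The main mixed model omits the gait-speed stratum used to randomise and names no within-person covariance beyond a participant random effect

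*Supplement*

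**What the plan says.** Protocol version 1.4, section 10.6, assigns participants "in a 1:1 ratio, stratified by whether a slower" or faster walker, in blocks of 4 or 6 within each stratum.

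Section 10.1 models change from baseline on arm, visit and their interaction, with "baseline value of outcome as a fixed-effect covariate; and a subject random effect to account for multiple follow-up assessments". The Final Statistical analysis plan keeps this model for each continuous outcome: "baseline value of outcome as a fixed effect covariate; and a participant random effect". Wear time is added for accelerometer outcomes only. Stratum and stratum by intervention appear when the analysis is repeated to obtain stratum-specific findings, and the Summary of Changes describes that repeat as the subgroup analysis.

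The Original statistical analysis plan sets alpha at 0.05 "for the 12-week gait speed means contrast will be considered the formal test of the primary hypothesis". The 24- and 36-week contrasts from the same model serve the secondary hypotheses. No section names a residual covariance structure, a robust standard error or a degrees-of-freedom method.

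**The concern.** Stratified randomisation balances the arms on the stratum. If the stratum predicts the outcome and the model leaves it out, that variation stays in the residual, and the model's standard error overstates the real sampling variation of the arm difference. For gait speed, the baseline covariate recovers most of this but not all, because the stratum comes from a timed 4-metre walk and the outcome from a computerised walkway. For LLFDI, strength, flexibility and actigraphy, the outcome's own baseline may say little about the stratum.

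The second part concerns the visits. If a participant random effect is the only within-person term and residuals take the software default, all three visits share one variance. Each visit has its own contrast, so a pooled variance misstates the standard error wherever that visit's variance differs from the average. Unequal variance is plausible: supervised training ends at week 12, behavioural sessions thin out over the next 12 weeks, and the visit window widens from 2 weeks either side to minus 2/plus 4 weeks. None of this shows that it occurs.

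**Working it through.** **Inputs.** Two-sided testing (section 10.5: "detect statistical significance in two-tailed tests conducted at the" 0.05 level). From section 10.5.1: a difference of 0.10 m/s ("a meaningful change in gait speed is approximately 0.10 m/s"), SDs ("baseline gait speed is 0.17 m/s and baseline to follow-up change in gait speed is 0.15 m/s") and sample size ("With the proposed number of 124 in each intervention"), with 62 per arm per stratum. From section 2.4, pilot gains (timing and coordination / standard): 0.21 / 0.14 m/s in slow walkers and 0.13 / 0.05 m/s in fast walkers.

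**The plan's own power.** Power = Φ(0.10 / SE − 1.96), with SE = 0.15 × √(2/n).
- n = 124: SE = 0.01905, power 99.95% (stated: above 99%).
- n = 62: 96.0% (stated 96%).
- n = 52: 92.5% (stated 92%).
- n = 49: 91.0%, or 90.4% by noncentral t (stated 90%).

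The stated figures reproduce.

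**Omitted stratum, no help from baseline.** The slow-minus-fast gap in gain is 0.21 − 0.13 = 0.08 and 0.14 − 0.05 = 0.09 m/s, midpoint 0.085. With equal strata the between-stratum variance is (gap/2)². The ratio of model SE to true SE is √(1 + (gap/2)² / 0.15²), and true alpha is 2 × Φ(−1.96 × ratio).

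| Gap (m/s) | SE ratio | True alpha |
|---|---|---|
| 0.08 | 1.035 | 0.043 |
| 0.085 | 1.039 | 0.042 |
| 0.09 | 1.044 | 0.041 |

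**Omitted stratum, baseline in the model.** A simulation used 6,000 replicates, 62 per arm per stratum, three visits, complete data and a gap of 0.085. Assumed: within-person correlation 0.6; baseline means 0.85 and 1.08 m/s, with SDs 0.10 and 0.06 plus measurement noise of 0.05.

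| Case | Model | Mean SE | Empirical SD | Ratio | Type I error |
|---|---|---|---|---|---|
| Gait speed | no stratum | 0.01935 | 0.01917 | 1.01 | 0.050 |
| Gait speed | stratum | 0.01905 | 0.01905 | 1.00 | 0.052 |
| Baseline unrelated to stratum | no stratum | 0.01983 | 0.01903 | 1.04 | 0.040 |
| Baseline unrelated to stratum | stratum | 0.01907 | 0.01902 | 1.00 | 0.047 |

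**Common variance across visits.** With complete data (the plan imputes), a random-intercept model uses the mean of the three visit variances at each visit. The SE ratio at a visit is √(mean variance / variance at that visit). The document gives only 0.15 m/s, so the trends below are assumed.

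Rising SDs 0.15 / 0.165 / 0.18: mean variance = (0.0225 + 0.027225 + 0.0324) / 3 = 0.027375.
- Week 12: √(0.027375 / 0.0225) = 1.10, alpha 0.031.
- Week 36: √(0.027375 / 0.0324) = 0.92, alpha 0.072.

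Falling SDs 0.15 / 0.135 / 0.12: mean variance = (0.0225 + 0.018225 + 0.0144) / 3 = 0.018375.
- Week 12: √(0.018375 / 0.0225) = 0.90, alpha 0.077.
- Week 36: √(0.018375 / 0.0144) = 1.13, alpha 0.027.

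Equal SDs: ratio 1.00 and alpha 0.05 at every visit.

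Simulation at week 12 agrees. Without the stratum, type I error was 0.028 (rising) and 0.075 (falling). With the stratum and a visit-specific variance it was 0.052 and 0.055. Power for 0.10 m/s at 12 weeks was at least 99.9% in every scenario.

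**The case against.** The strongest reply has four parts.

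1. *The stratum hardly matters for the primary test.* This stands. Baseline speed carries most of it, the remaining error is about 1% and conservative, and power exceeds 99%. A reader might carry the 3.5 to 4.4% inflation over to gait speed, or convert it into participants (6.6 to 8.3% of 248, about 16 to 20). The documents do not support that, because the model already adjusts for baseline speed.

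2. *The 0.08 to 0.09 m/s gap is not a stratum effect within one trial.* This also stands. It compares two pilots with different eligibility and programme content, and for the non-gait outcomes no stratum effect is given at all. The 4% is therefore conditional.

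3. *Equal variance is an inference.* This stands in part. The plan does not state the constraint and refers to a published methods paper for details, which is not among the documents. But a participant random effect is the only structure named, and compound symmetry is its ordinary reading.

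4. *The plan already covers this.* This holds only in part. The repeat model has the stratum but serves the subgroup question. The Box-Cox check addresses residual assumptions and would not necessarily cure variances that differ by visit. The Original statistical analysis plan fixes the main model to keep it predictable. That argues against covariates chosen after seeing baseline imbalance, not against a stratum known before randomisation.

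**Conclusion.** The concern holds as a modest improvement to the main model, with two parts of different standing.

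The missing stratum is plain in the text. Its effect is conservative: SE about 1% too large for gait speed, and up to about 4% for outcomes whose baseline does not carry the stratum, if the cross-pilot gap applies to them on a comparable scale.

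The covariance is under-specified. A reader might infer that the standard errors are wrong, or that the 36-week test is too liberal. The documents support neither. They give one SD of change and none by visit, so error is possible but not shown, and its direction is unknown. Under the assumed trends of plus or minus 20%, alpha runs from 0.031 to 0.077 at 12 weeks and from 0.027 to 0.072 at 36 weeks. With equal SDs the error is nil.

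The stated power does not depend on either part.

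**What to change.** Add the randomisation stratum, as recorded at randomisation, as a fixed effect in the main model for every outcome. Replace the lone participant random effect with an unstructured 3×3 within-person covariance and Kenward-Roger degrees of freedom, fitted in each imputed data set and pooled as now. State the covariance structure actually used and report the SD of change by visit, which would show whether the second part matters.

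The Final Statistical analysis plan reports the analysis as already done. The re-run should therefore appear at least as a sensitivity analysis beside the pre-specified model.

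Cost: 1 degree of freedom for the stratum, 4 more covariance parameters (6 instead of 2) with 248 participants, and a re-run of each outcome. No new data are needed.

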### **Summary of Changes**

There were three unplanned post-completion deviations, all relatively minor or necessary:

- (1) In the subgroup analysis, instead of repeating the main analysis simply stratified by baseline slow/fast stratum, we had included it as an additional fixed effect with interaction terms. This was done so that we could obtain statistical significance of differential findings in the slow and fast strata.
- (2) Actigraphy physical activity variables were analyzed separately with respect to multiple imputation from other outcomes due to they not being required prior to randomization, and the resulting large number without that data.
- (3) Statistical models for actigraphy physical activity variables included wear time as an additional covariate, in keeping with the standard practice in the field.

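### As written, the final stratum model forces the slow–fast difference in treatment effect to be equal at 12, 24 and 36 weeks, so the 12-week stratum results borrow from the later visits

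*Supplement*

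**What the plan says.** The final statistical analysis plan specifies a linear mixed model for change from baseline with "intervention arm, follow-up time point and their interaction as fixed effects", the baseline value as a covariate and a participant random effect. For the strata it says: "We repeated the analysis with gait speed stratum and stratum" × intervention "as additional fixed effects to obtain stratum-specific findings". No other stratum term is named.

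This replaced a different analysis. In the Original statistical analysis plan, "we will repeat the above mixed model analysis entirely, but with" stratification by baseline gait speed; protocol version 1.4, section 10.1, says the same. The Summary of Changes, deviation (1), explains that "instead of repeating the main analysis simply stratified by baseline slow/fast stratum, we had included it as an additional fixed effect with interaction terms", so that a difference between the strata could be tested. It does not say which interactions were fitted.

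Hypothesis 1.2 (protocol section 1.1) is that the programs differ in both slower and faster walkers at 12 weeks. Protocol section 10.1 states: "Tests of significance for gait speed outcome at 12 weeks in each of the two strata will be considered formal tests" of that hypothesis.

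**The concern.** A model with arm × time and stratum × arm, but no stratum × arm × time, has one coefficient for how the treatment effect differs between slow and fast walkers. That coefficient applies at every visit and is estimated from all three. If the true slow–fast gap changes between 12 and 36 weeks, the later data pull the 12-week estimate in each stratum away from its own 12-week value, by equal amounts in opposite directions. The stratum × intervention p-value likewise tests the visit-averaged gap, not the gap at 12 weeks.

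Refitting the whole model within each stratum carries no such restriction. The change therefore altered what the 12-week stratum contrasts estimate as well as adding a test of difference, and the Summary of Changes does not mention this.

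**Working it through.** **Inputs from protocol sections 10.5 and 10.5.1.** SD of change σ = 0.15 m/s; meaningful difference 0.10 m/s; 62 randomised and 55 expected 12-week completers per arm per stratum; two-sided α = 0.05. **Assumed, because the documents give neither:** the between-visit correlation ρ and the course of the effects after 12 weeks.

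**The plan's own figure.** For a separate comparison within a stratum, SE = σ√(2/n). With n = 62 this is 0.15 × √(2/62) = 0.0269, and power is Φ(0.10/0.0269 − 1.96) = 96%, as stated. With n = 52 and 49 the noncentral t gives 92.0% and 90.4%, matching the stated 92% and 90%. The protocol's stratum power thus rests on comparisons specific to each stratum and visit.

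**What the model as written estimates.** Let d(s,t) be the treatment effect in stratum s at visit t, and g(t) = d(slow,t) − d(fast,t), with mean ḡ over the three visits. With equal strata and complete data:

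- slow, 12 weeks: ½[d(slow,12) + d(fast,12)] + ½ḡ
- fast, 12 weeks: ½[d(slow,12) + d(fast,12)] − ½ḡ

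The shift from the true value is ½[ḡ − g(12)] in slow walkers and the reverse in fast walkers. It is zero when g is constant.

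| Assumed true effects at 12/24/36 weeks (m/s) | g(t) | ḡ | Model's 12-week slow, fast | Shift |
|---|---|---|---|---|
| Pilot values, constant: slow 0.07, fast 0.11 | −0.04 throughout | −0.04 | 0.07, 0.11 | 0 |
| Pilot values, both falling linearly to half by week 36 | −0.04/−0.03/−0.02 | −0.03 | 0.075, 0.105 | 0.005 |
| Pilot values, both falling linearly to zero | −0.04/−0.02/0 | −0.02 | 0.08, 0.10 | 0.01 |
| Both 0.07 at 12 weeks; slow sustained, fast falling to zero | 0/0.035/0.07 | 0.035 | 0.0875, 0.0525 | 0.0175 |
| Slow 0.10/0.05/0; fast 0.10 throughout | 0/−0.05/−0.10 | −0.05 | 0.075, 0.125 | 0.025 |
| Slow 0.10/0.05/0; fast zero throughout | 0.10/0.05/0 | 0.05 | 0.075, 0.025 | 0.025 |

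The pilot values are the adjusted group differences in protocol section 2.4. With the planned 10/15/20% dropout and ρ = 0.5, the fifth row becomes 0.077 and 0.123. A model with the three-way term returns the true values in every row. Adding stratum × time alone leaves the arm contrasts unchanged in this balanced design.

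**Standard errors, 55 per arm per stratum at each visit.**

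- Model as written: variance (σ²/n)(4 + 2ρ)/3. For ρ = 0.5, SE = √(0.0225/55 × 5/3) = 0.0261; for ρ = 0.7, √(0.0225/55 × 1.8) = 0.0271.
- With the three-way term: 0.15 × √(2/55) = 0.0286, larger by a factor of 1.05 to 1.10.
- 12-week gap with the three-way term: 2σ/√n = 0.3/√55 = 0.0405. Visit-averaged gap as written: 0.0405 × √((1 + 2ρ)/3), which is 0.0330 at ρ = 0.5 and 0.0362 at ρ = 0.7.

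**Consequences in the last row, for ρ = 0.5–0.7.** In fast walkers, whose true effect is zero, 0.025/0.0261 = 0.96 and 0.025/0.0271 = 0.92, giving two-sided rejection of 16% and 15%. In slow walkers, power is Φ(0.075/0.0261 − 1.96) = 82% down to 79%, against Φ(0.10/0.0286 − 1.96) = 94% with the three-way term.

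**The case against.** The strongest reply is that the fitted model is not certain. The Summary of Changes says "we had included it as an additional fixed effect with interaction terms", in the plural, and the final plan is a condensed paragraph that refers to the published protocol for details. More terms may have been fitted. This stands, and it makes the bias conditional on the wording being complete. It does not remove the need to act, since the final plan would then be describing the wrong model.

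Second, the bias needs a gap that changes over visits. A reader might infer that the delayed- and sustained-effect aims predict such a change. They do not: section 1.2 concerns standard-plus against standard overall and says nothing about slow and fast walkers having different time courses. The constant-gap assumption is unstated and untested, but the documents do not contradict it.

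Third, a reader might take the 15–16% false-positive rate as what to expect. It belongs to one extreme path, with no effect at all in fast walkers and complete fading in slow walkers. The pilot data showed the larger group difference in faster walkers, and proportional fading from those values shifts the estimates by only 0.005–0.01 m/s.

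Fourth, the Original statistical analysis plan calls only the overall 12-week contrast the formal test of the primary hypothesis, and the Summary of Changes treats the strata as a subgroup analysis. That weakens the confirmatory weight of hypothesis 1.2. Protocol version 1.4 still labels its tests formal, however, and sizes the trial for them.

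Finally, pooling the gap over visits gains precision and the change was disclosed with a reason. Both are true, but a three-way model also gives a test of difference, and gives it at 12 weeks.

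**Conclusion.** The point holds for the model as described, and should be fixed. The 12-week contrast in each stratum is unbiased only if the slow–fast gap is the same at all three visits, a restriction that the separate fits did not impose. The shift ranges from nil (constant gap), through 0.005–0.01 m/s (pilot differences fading in proportion), to 0.025 m/s, a quarter of the meaningful change, if an effect of 0.10 m/s fades to zero in one stratum only. These sizes rest on assumed paths, equal strata and a random-intercept structure.

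It would go too far to say that the stratum estimates carry no 12-week information: arm × time is in the model, and only the stratum deviation is pooled over visits. Nor does leaving out stratum × time do harm by itself; the missing three-way term does. The overall 12-week test of hypothesis 1.1 is unaffected.

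**What to change.** Add stratum × time and stratum × intervention × time, using the randomisation stratum. The first is needed so that the three-way term sits in a complete hierarchy. Take the 12-week within-stratum contrasts and the 12-week interaction test for hypothesis 1.2 from that model. Report the pre-specified separate-stratum fits beside it; these also let the baseline slope and variance components differ by stratum. If the visit-averaged interaction is kept, label it as such. If the extra terms were already fitted, correct the final plan to list them.

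The cost is one sentence and one re-run, with no new data. For ρ = 0.5–0.7 the 12-week stratum SE is about 5–10% larger (0.0286 against 0.0261–0.0271). The 12-week interaction SE is about 12–22% larger than that of the visit-averaged test (0.0405 against 0.0330–0.0362).
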